**Legend:**

**eTable 1:** Incidence of COVID-19 after post exposure prophylaxis with HCQ and placebo in participants  
in whom RTPCR could be performed

**eTable 2:** COVID-19 related symptoms of the study population

eTable 1: Incidence of COVID-19 after post exposure prophylaxis with HCQ and placebo in participants in whom RTPCR could be performed

| Outcomes (N=1156)                     | Placebo/Control group (N=587) | PEP/HCQ group (N=569) | P value |
|---------------------------------------|-------------------------------|-----------------------|---------|
| COVID-19 * (N=47)                     | 24 (4.1%)                     | 23 (4.0%)             | 0.968   |
| Definite COVID-19 a (N=37) | 21 (3.6%)                     | 16 (2.8%)             | 0.460   |
| Probable COVID-19 (N=10)              | 3 (0.5%)                      | 7 (1.2%)              | 0.187   |

\* Total absolute risk reduction was -0.1% point with number needed to treat (NNT) was 1000 and relative risk was 0.98 (95% confidence interval, 0.55 to 1.77).

a Total absolute risk reduction was -0.8% point with number needed to treat (NNT) was 125 and relative risk was 0.78 (95% confidence interval, 0.40 to 1.51).

eTable 2 : COVID-19 related symptoms of the study population

| COVID-19 symptoms  | Control group (N=594) | PEP/HCQ group (N=574) | P value |
|--------------------|-----------------------|-----------------------|---------|
| Fever (N=23)       | 13 (2.2%)             | 10 (1.7%)             | 0.583   |
| Sore throat (N=15) | 8(1.3%)               | 7(1.2%)               | 0.847   |
| Cough (N=15)       | 8(1.3%)               | 7(1.2%)               | 0.847   |
| Myalgia (N=5)      | 2(0.3%)               | 3(0.5%)               | 0.627   |
| Head ache (N=3)    | 2 (0.3%)              | 1 (0.2%)              | 0.583   |
| Diarrhoea (N=1)    | 0 (0.0%)              | 1 (0.2%)              | .309    |
| Joint pain (N=1)   | 1 (0.2%)              | 0 (0.0%)              | 0.325   |
| Sneezing (N=1)     | 1 (0.2%)              | 0 (0.0%)              | 0.325   |
| Body ache (N=1)    | 0 (0.0%)              | 1 (0.2%)              | 0.309   |

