**Sample size & statistical analysis:**

As per recently concluded our institutional pilot study, the incidence of COVID-19 was significantly ( $P = 0.033$ ) lower in the PEP group (10.6%) that received HCQ prophylaxis compared with the control group (19.5%). The total absolute risk reduction for the incidence of COVID-19 in participants received PEP with HCQ was  $-8.9\%$  points [13]. Anticipating at least 20% incidence of COVID-19 in control group as compared to 10% incidence rate in PEP group the total sample size will be around 400 (200 each group), when there will be 80% (power) chance of detecting a significant difference between the two groups at a one-sided 0.05 significance level ( $\alpha$ -error of 5%). Anticipating 10% dropout we will try to recruit total 440 participants for the study. However as per protocol, after following strict inclusion and exclusion criteria the final sample size for the data analysis may reduce further. Final power of the study may be recalculated after getting actual response/outcome at the end of the clinical trial through post-hoc statistical power analysis. Randomization will be done with the help of computer generated random number in a block randomization pattern in a block of 10 patients (5:5). Randomization and treatment concealment will be done by the pharmacologist. The data will be managed in data base system through Microsoft Excel and statistical analysis will be performed by SPSS 21.0 version. The parametric data will be

analyzed by paired or unpaired “t”-test and the binominal/categorical endpoints will be analyzed with non-parametric chi-square test with yet’s correlation and the proportions will be compared by Fisher’s exact test. The relative risk (RR) and number needed to treat (NNT) will be determined for the safety and risk assessment. The p-value less than 0.05 will be considered statistical significant (95% CI).

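### eTable 1 prints odds ratio limits as relative risk limits and takes its NNTs from rounded percentages; the P values in eTables 1 and 2 come from neither planned test

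*Protocol*

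**What the plan says.** The analysis paragraph of the Protocol (Part II, section 6, Sample size & statistical analysis) fixes the effect measures: "The relative risk (RR) and number needed to treat (NNT) will be determined for the safety and risk assessment". For categorical endpoints it names a "chi-square test with yet’s correlation and the proportions will be compared by Fisher’s exact test". The first of these can only sensibly mean Yates' continuity correction. An uncorrected chi-square is not mentioned. The same paragraph sets the threshold: "The p-value less than 0.05 will be considered statistical significant (95% CI)".

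eTable 1 (Protocol, Legend) covers participants in whom RTPCR could be performed. Its columns are "Placebo/Control group (N=587)" and "PEP/HCQ group (N=569)". For COVID-19 the footnote states that the "number needed to treat (NNT) was 1000 and relative risk was 0.98 (95% confidence interval, 0.55 to 1.77)". For definite COVID-19 it states that the "number needed to treat (NNT) was 125 and relative risk was 0.78 (95% confidence interval, 0.40 to 1.51)". The printed P values are 0.968 (COVID-19), 0.460 (definite) and 0.187 (probable). eTable 2 lists nine symptoms with P values, on 594 control and 574 HCQ participants.

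**The concern.** The table prints its counts, so each derived figure can be checked. A relative risk from these counts does not have the printed limits. An NNT of exactly 1000 beside a difference of 0.1 points suggests division by a rounded number. P values near 0.31 to 0.33 for rows with one event in one arm and none in the other are too small for either planned test.

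The three outcomes in eTable 1 are the ones the protocol lists as primary. A mislabelled interval or an NNT that is wrong by a factor of two can be carried into a pooled analysis by a reader who trusts the label. A bare NNT also reads as a benefit, when the data are equally compatible with harm.

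**Working it through.** **Inputs (eTable 1).** COVID-19: HCQ 23/569 = 4.0422%, placebo 24/587 = 4.0886%. Definite: HCQ 16/569 = 2.8120%, placebo 21/587 = 3.5775%. Probable: HCQ 7/569, placebo 3/587. From eTable 2: symptom counts on 574 (HCQ) and 594 (control).

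**1. Ratio measures.**
RR = (a/n1)/(b/n0), with SE(ln RR) = √(1/a − 1/n1 + 1/b − 1/n0).
OR = a(n0−b)/[b(n1−a)], with SE(ln OR) = √(1/a + 1/(n1−a) + 1/b + 1/(n0−b)).
Limits are estimate × exp(±1.96 SE).

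| Outcome | Printed as RR | RR from counts | OR from counts |
|---|---|---|---|
| COVID-19 | 0.98 (0.55 to 1.77) | 0.989 (0.565 to 1.731), SE 0.2858 | 0.988 (0.551 to 1.772), SE 0.2979 |
| Definite | 0.78 (0.40 to 1.51) | 0.786 (0.414 to 1.491), SE 0.3266 | 0.780 (0.403 to 1.510), SE 0.3372 |

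All four printed limits equal the OR limits to two decimals. None equals the RR limit. The point estimates are less telling. For COVID-19 both measures round to 0.99, so 0.98 is either a truncation or the ratio of rounded percentages (4.0/4.1 = 0.976). For definite COVID-19, 0.78 fits the OR but also 2.8/3.6 = 0.778.

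**2. NNT = 1/(placebo rate − HCQ rate).**
The printed values reproduce from one-decimal percentages: 1/(0.041 − 0.040) = 1000 and 1/(0.036 − 0.028) = 125.
From the counts:
- COVID-19: difference 0.0464 points, NNT = 1/0.000464 ≈ 2155, which is 2155/1000 ≈ 2.2 times the printed value.
- Definite: difference 0.7656 points, NNT = 1/0.007656 ≈ 131.

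**3. Interval for the risk difference (HCQ − placebo, Newcombe's method from Wilson limits, in percentage points).**
- COVID-19: Wilson limits are 2.708 to 5.992 (HCQ) and 2.763 to 6.011 (placebo). Lower: −0.046 − √[(4.042−2.708)² + (6.011−4.089)²] = −2.39. Upper: −0.046 + √[(5.992−4.042)² + (4.089−2.763)²] = +2.31. On the NNT scale this runs from 1/0.0239 ≈ 42 (benefit) through infinity to 1/0.0231 ≈ 43 (harm).
- Definite: Wilson limits are 1.738 to 4.519 (HCQ) and 2.352 to 5.407 (placebo). Lower: −0.766 − √[(2.812−1.738)² + (5.407−3.578)²] = −2.89. Upper: −0.766 + √[(4.519−2.812)² + (3.578−2.352)²] = +1.34.

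**4. P values (two-sided).**

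| Row | Printed | Pearson, uncorrected | Yates | Fisher | Smallest expected count |
|---|---|---|---|---|---|
| COVID-19 | 0.968 | 0.968 | 1.000 | 1.000 | 23.1 |
| Definite | 0.460 | 0.460 | 0.567 | 0.506 | 18.2 |
| Probable | 0.187 | 0.187 | 0.316 | 0.218 | 4.92 |
| Fever | 0.583 | 0.583 | 0.735 | 0.676 | 11.3 |
| Sore throat, cough | 0.847 | 0.847 | 1.000 | 1.000 | 7.4 |
| Myalgia | 0.627 | 0.627 | 0.969 | 0.682 | 2.5 |
| Headache | 0.583 | 0.583 | 1.000 | 1.000 | 1.5 |
| Diarrhoea, body ache | 0.309 | 0.309 | 0.986 | 0.491 | 0.49 |
| Joint pain, sneezing | 0.325 | 0.325 | 1.000 | 1.000 | 0.49 |

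Every printed value is the uncorrected Pearson result. None matches either planned test.

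**The case against.** The strongest reply is that nothing of substance moves. The RR limits shift from 0.55–1.77 to 0.56–1.73 and from 0.40–1.51 to 0.41–1.49. The definite NNT goes from 125 to 131. The twofold NNT error is a change from 0.1 to 0.05 points inside an interval about 4.7 points wide. No P value falls below 0.05 under any of the three tests. All of this stands, and it limits the weight of the point.

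Several stronger readings are tempting and are not supported:

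- A reader might infer that these are the trial's main results. eTable 1 is restricted to 1156 RTPCR-tested participants, against 594 + 574 = 1168 in eTable 2. The protocol counts symptomatic participants without an RTPCR result as probable cases, so its primary outcome is not restricted in this way. The full-population effect estimates are not in the document, and whether they share these faults is unknown.
- A reader might infer that the point estimates are plainly odds ratios. Only the limits show this; 0.98 is neither measure rounded, and 0.78 has two possible origins.
- A reader might infer that all the P values are invalid. With smallest expected counts of 23 and 18, uncorrected Pearson is adequate for COVID-19 and definite COVID-19. There the fault is departure from the stated test. Adequacy is in doubt only in the sparse rows.
- A reader might infer that an NNT must be withheld when the interval includes zero. That is a reporting convention. The protocol promises an NNT and no interval for it.

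The reply that these are results and not design is true, but the tables are part of the protocol document and disagree with its counts and its analysis paragraph.

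**Conclusion.** The point holds as a minor correction of stated figures. The limits labelled relative risk are odds ratio limits, the COVID-19 estimate of 0.98 is wrong for either measure, both NNTs come from rounded percentages (the COVID-19 one is too small by a factor of about 2.2), and the P values in both tables come from a test the protocol does not name. The null conclusion is unchanged, and design, sample size and outcome definitions are not affected.

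This rests on the printed counts being correct, on standard log-scale intervals for RR and OR, and on reading the garbled test name as Yates' correction. The protocol does not say clearly which of its two tests applies where, but the printed values match neither.

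**What to change.** - Replace the eTable 1 footnotes with the planned relative risks: COVID-19 0.99 (95% CI 0.56 to 1.73) and definite COVID-19 0.79 (0.41 to 1.49). Relabelling the existing figures as odds ratios is not enough: it would keep an incorrect 0.98 and depart from the measure the protocol names.
- Report the risk difference with its 95% CI: COVID-19 about −0.05 points (−2.4 to +2.3), definite about −0.77 points (−2.9 to +1.3).
- If an NNT is given, compute it from unrounded rates (about 2155 and 131) and print it beside that interval.
- Recompute the P values in both tables with the planned tests, using Fisher's exact test for sparse rows (for example probable COVID-19 0.218, diarrhoea 0.491). Correct the test name in the analysis paragraph and state which test applies where.

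The cost is a short recalculation of a few table entries from counts already printed; no new data are needed.

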## **7. Project summary:**

Novel corona virus (SARS-CoV-2) epidemic which started from Wuhan in China is now a well established pandemic affecting more than 57 million people worldwide with more than 1.3 million of mortality. COVID-19 affected more than 9 million of people with more than 130 thousand death in India. If adequate preventive and therapeutic measures are not taken, India has very high risk of affecting million of more people with high mortality because of the large population along with very high population density. At present there are no definitive therapeutic drugs or vaccine available for the treatment and prevention of SARS-CoV-2 infection. Symptomatic and supportive care are being given to COVID-19 cases along with isolation and quarantine measure are being taken for the suspected individual at risk for COVID-19 to limit the spread of the SARS-CoV-2 infection . Among the all the drugs being used for the treatment of COVID-19, hydroxychloroquine (HCQ), has given some rays of hope to battle against this deadly pandemic. HCQ has some anti viral effect against SARS-CoV in vitro. HCQ is quite safe and being used in rheumatology patients for lifelong without much side effect, so it allow for higher dose without any significant side effects and drug-drug interaction. Recently published clinical trial suggested HCQ can be used for the therapeutic purpose of the SARS-CoV-2 infection and many governments have endorsed that due to lack of any other better alternative drugs. Indian council of medical research (ICMR) has advised for HCQ prophylaxis for the people who are at risk for developing SARS-CoV-2 infection, all asymptomatic health care workers involved in taking care of suspected or confirmed COVID-19 cases and all asymptomatic household contacts of laboratory confirmed COVID-19 cases. This encouraged us to conduct an open level clinical trial on HCQ as post exposure prophylaxis (PEP) for the prevention of COVID-19 in asymptomatic high risk house hold contact of the laboratory confirmed COVID-19 cases. The result was very promising showing absolute risk reduction of around 9% in participant who received PEP with HCQ as compared to the control group and there was no serious adverse event. But there is still conflicting scientific data to prove or disprove the efficacy of HCQ for the treatment and prophylaxis for SARS-CoV-2 infection. Being a tertiary care centre we are catering many states which include Punjab, hariyana, himachal Pradesh, Uttara khand, Uttar Pradesh. This put our institute to handle highest burden of suspected cases of SARS-CoV-2 in northern India. So we have subsequently planned this double blind clinical trial to evaluate the efficacy of HCQ as PEP for the prevention of COVID-19 in asymptomatic individuals who are at risk for SARS-CoV-2 infection. As a research institute of national as well as international interest, it is a great opportunity for us to produce such a robust data which can be utilized in reforming national and international guidelines for the battle against of COVID-19 pandemic. The asymptomatic individual with direct contact with laboratory confirmed COVID-19 cases will be randomized into one PEP group and one control/placebo group as per inclusion and exclusion criteria. Individual who will not give consent for HCQ prophylaxis and those

with contraindication for HCQ therapy like, hypersensitivity to HCQ or 4-aminoquinolone derivatives, patients with known retinopathy, cardiac arrhythmia, G6PD deficiency, psoriasis and pregnancy will be excluded from the study. All symptomatic individual and all health care workers related to suspected or proven COVID-19 and who received CoVID-19 vaccine will be excluded from the study. The PEP group will receive tablet HCQ 400 mg q 12 hourly on day one followed by 400 mg once weekly for 3 weeks (total cumulative dose of 2000 mg). The control group will receive placebo instead of HCQ. Both the groups will receive standard care of therapy in the form of home quarantine for 2 weeks along with social distancing and personal hygiene. They will be followed up for 4 weeks telephonically or physically as and when required and will be enquired regarding development of any COVID-19 symptoms like fever, cough, sore throat, shortness of breath, diarrhoea, myalgia. During follow up nasopharyngeal swab of the participants will be taken for processing reverse transcription polymerase chain reaction (RTPCR) for the detection of SARS-CoV-2 RNA to confirm the CoVID-19. Samples for RTPCR will be taken when any asymptomatic participants becomes symptomatic and by the 5-14 days of contact in asymptomatic participants through in-hospital visit at the institute's COVID-19 screening clinic at Emergency medical out patients department (EMOPD) or communicable disease ward isolation. The participants with new onset COVID-19 will be managed as per institute's COVID-19 management protocol and the participants needing admission will be given best possible medical care in the institute's SARI/Nehru extension COVID ward under isolation. Only the participant with RTPCR positive for SARS-CoV-2 and with or without symptoms will be defined as definite COVID-19 case. The participant with new onset symptoms, but RTPCR negative for SARS-CoV-2 or cannot be performed for any reason will be defined as probable COVID-19 case. Asymptomatic participants with negative RTPCR will be defined as non-COVID case. The incidence of COVID-19 will be compared between the PEP and control groups. Department of internal medicine (Emergency) will be taking care of screening, enrolment, patients management, follow up and data analysis. Department of pharmacology will take care of randomization & blinding and adverse events monitoring. Department of Virology will take care of molecular diagnosis of COVID-19 by RTPCR as and when required. Department of Community medicine & school of public health will take care of contact tracing and information to the local IDSP.

## **Part-II**

### **1. Research hypothesis:**

There are no definitive proven therapeutic drugs for SARS-CoV-2 infection management. Among the various drugs used for the treatment of SARS-CoV-2, HCQ has given some rays of hope to battle against this deadly pandemic due to its anti viral effect against SARS-CoV in vitro. Indian council of medical research (ICMR) has advised for HCQ prophylaxis for the people who are at risk for developing SARS-CoV-2 infection, all asymptomatic health care workers involved in taking care of suspected or confirmed COVID-19 cases and all asymptomatic household contacts of laboratory confirmed COVID-19 cases. This encouraged us to conduct an open level clinical trial on HCQ as post exposure prophylaxis (PEP) for the prevention of COVID-19 in asymptomatic high risk house hold contact of the laboratory confirmed COVID-19 cases. The result was very promising showing absolute risk reduction of around 9% in participant who received PEP with HCQ as compared to the control group and there was no serious adverse event. But there is still conflicting scientific data to prove or disprove the efficacy of HCQ for the treatment and prophylaxis for SARS-CoV-2 infection. This study will evaluate the efficacy of HCQ as PEP to prevent SARS-CoV-2 infection in asymptomatic at risk individual.

### **2. Background and rational of the study:**

Novel corona virus (SARS-CoV-2) epidemic which started from Wuhan in China is now a well established pandemic affecting more than 57 million people worldwide with more than 1.3 million of mortality [1]. After Italy, Spain, Germany, United Kingdom and Brazil have taken over from China in term of the burden of mortality, India is the next epicentre of this pandemic just behind USA. COVID-19 affected more than 9 million of people with more than 130 thousand of death in India [2]. The clinical presentation of the COVID-19 varies from asymptomatic cases and mild symptoms of fever, cough, sore throat, headache, myalgia, nasal congestion, diarrhea to severe pneumonia, acute respiratory distress syndrome (ARDS) requiring mechanical ventilation and even multi-organ dysfunction syndrome (MODS), sepsis leading to death [3]. If adequate preventive and therapeutic measures are not taken, India has very high risk of affecting million of people with high mortality because of the large population, very

high population density and ongoing relaxation of the previously imposed lockdown. At present there are no definitive therapeutic drugs or vaccine available for the treatment and prevention of SARS-CoV-2 infection. Symptomatic and supportive care are being given to COVID-19 cases along with isolation and quarantine measure are being taken for the suspected individual at risk for COVID-19 to limit the spread of the SARS-CoV-2 infection [4].

Presently many scientist and doctors are recommending many existing available drugs (Ribavirin, lopinavir, Remdesivir, chloroquine, hydroxychloroquine) for SARS-CoV-2 infection for therapeutic and as well as prophylactic purpose [5,6]. Among which hydroxychloroquine sulphate (HCQ), a chloroquine analogue has given some rays of hope to battle against this deadly pandemic [7]. In vitro studies showed that HCQ had potent anti viral effect against SARS-CoV through mechanism targeted at the host cell [8-10]. HCQ is quite safe drugs as it is being used in rheumatology patients for lifelong therapy without much side effect, so it allow for higher dose without any significant side effects and drug-drug interaction [11]. Recently published clinical trial suggested HCQ can be used for the therapeutic purpose of the SARS-CoV-2 infection [7]. ICMR has advised for HCQ prophylaxis for the people who are at risk for developing SARS-CoV-2 infection, all asymptomatic health care workers involved in taking care of suspected or confirmed COVID-19 cases and all asymptomatic household contacts of laboratory confirmed COVID-19 cases [12]. This encouraged us to conduct an open level clinical trial on HCQ as PEP for the prevention of COVID-19 in asymptomatic high risk house hold contact of the laboratory confirmed COVID-19 cases. The result was very promising showing absolute risk reduction of around 9% for prevention of COVID-19 in participant who received PEP with HCQ as compared to the control group which did not receive HCQ and there was no serious adverse event [13]. But there is still conflicting scientific data to prove or disprove the efficacy of HCQ for the treatment and post exposure chemo-prophylaxis for SARS-CoV-2 infection management. Recently published study proposed that HCQ was not useful as post exposure prophylaxis (PEP) for prevention of COVID-19 in at risk individual [14]. But in this study majority of the participants were health care workers (HCW). Recently newer studies have come in support of HCQ for the potential preventive measure against COVID-19 [13, 15].

The household direct contacts of the COVID-19 patients are at the highest risk for SARS-CoV-2 infection. There is still lack of clinical trial regarding PEP with HCQ for the prevention of COVID-19 in non-HCW individuals who are at risk of SARS-CoV-2 infection. Being a tertiary care centre we are catering many states which includes Punjab, Haryana, Himachal Pradesh, Uttara Khand, Uttar Pradesh. This put our institute to handle highest burden of suspected cases of SARS-CoV-2 in northern India. So we have planned this randomised control clinical trial to evaluate the efficacy of HCQ as PEP for the prevention of COVID-19 in asymptomatic population who are at risk for SARS-CoV-2 infection. As a research institute of national as well as international interest, it is a great opportunity for us to produce such a robust data which can be utilized in reforming national and international guidelines for the battle against of COVID-19 pandemic.

